**3.2.2 Exclusion criteria**

(1) Those who have suffered from any serious acute illness within 8 weeks;

(2) Subjects with a history of active autoimmune disease or autoimmune disease requiring systemic treatment;

(3) Prior treatment/exposure to any other ICIs (e.g., PD-1, anti-PD-L1, anti-PD-L2, anti-CTLA4, etc.);

(4) Patients who have undergone the following treatments:

a) Received other anti-latent drug treatments within 30 days before enrollment;

b) Underwent radiotherapy or chemotherapy within 30 days before screening;

c) Received immunosuppressive therapy within 60 days before screening;

d) Received immunomodulatory agents (e.g., interleukins, interferons), hydroxyurea, or foscarnet within 60 days before screening;

e) Received an HIV vaccine or systemic cytotoxic chemotherapy within 60 days before screening;

f) Previously received IgG treatment;

g) Underwent blood transfusion or cell growth factor treatment within 90 days before screening;

h) Currently using or planning to use rifampicin, rifabutin, and other drugs during screening;

(5) Individuals whose laboratory examinations meet the following criteria:

a) ANC < 1.50× 109/L; Hb < 105 g/L (for men) or < 95 g/L (for women); platelets < 75× 109/μL; INR > 1× ULN;

b) SGPT/ALT > 1.5× ULN, SGOT/AST > 1.5× ULN, total bilirubin, direct bilirubin > 1.5× ULN, serum creatinine > 1.5× ULN, and the abnormalities are clinically significant;

c) Clinical significance of five thyroid function abnormalities, including T3, T4, FT3, FT4, and TSH;

d) Abnormal epinephrine test with clinical significance, including at least ACTH and cortisol;

e) Abnormal blood glucose and glycosylated hemoglobin tests with clinical significance;

(6) Abnormal and clinically significant findings on the twelve-lead electrocardiogram at the time of enrollment;

(7) Presence of interstitial changes on chest CT examination at the time of enrollment;

(8) Individuals with severe heart disease, symptomatic or asymptomatic arrhythmia;

(9) Patients co-infected with HBV, HCV, syphilis, other liver diseases, and diabetic patients;

(10) Individuals with active or suspected malignant tumors or a history of malignant tumors within the past five years (except for basal cell skin or cervical cancer in situ);

(11) Individuals with a history of tuberculosis or active tuberculosis;

(12) Subjects with psychiatric or substance abuse disorders known to interfere with their ability to meet study requirements;

(13) Individuals who have received immunomodulatory or immunosuppressive treatments (including any dose of IV/oral [PO] steroids, but excluding inhalation, topical, or local injection steroids) within 24 weeks before the first dose of the study drug;

(14) Pregnant and lactating women and individuals, both men and women, who plan to have children during the study;

(15) Individuals with mental health conditions or substance abuse issues that may interfere with the test;

(16) Patients who have used HDACI, such as valproic acid, butyrate, phenylbutyrate, etc., may be enrolled after a 28-day washout;

(17) Patients with severe cardiac insufficiency (New York Heart Association [NYHA] cardiac insufficiency class IV);

(18) Patients with a history of arterial thromboembolic events, including myocardial infarction, unstable angina; cerebrovascular accident, or transient ischemic attack, within six months before enrollment in treatment; standard treatment of uncontrolled hypertension (systolic blood pressure ≥ 150 mmHg or diastolic blood pressure ≥ 100 mmHg); and patients with cardiomyopathy;

(19) Patients with a significant QT/QTC interval prolongation during the screening period (e.g., repeated measurements show QTc interval > 450 milliseconds, or other conditions that may lead to TdP risk, such as heart failure; hypokalemia, familial long QT syndrome) or concurrent use of drugs that may prolong the QT/QTc interval;

(20) Individuals with known allergies or anti-drug antibodies to the drugs or excipients used in this trial;

(21) Individuals deemed unsuitable to participate in this trial by the researcher.

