**5 Clinical trial content**

**5.1 Sample size**

This study estimates that 12 participants will complete the trial, and the dropout rate will be controlled within 15%, so 15 participants are planned to be enrolled.

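### The platelet exclusion limit carries a per-microlitre unit that makes it a million times the per-litre reading, so the written criterion is not a usable threshold

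*Protocol*

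**What the plan says.** Section 3.2.2 of the protocol, item (5), opens with "Individuals whose laboratory examinations meet the following criteria", so a laboratory value that satisfies a listed condition keeps the person out. Sub-item a) then gives the haematology limits in one line. For neutrophils it states "ANC < 1.50× 109/L". For platelets it states "platelets < 75× 109/μL". In both quotes the 109 is 10^9 with a flattened superscript, which is an effect of text extraction and not an error in the plan.

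The exclusion criteria in the program summary repeat the platelet limit with the same unit. No other part of the protocol gives a platelet limit or corrects this one. The footnotes to Table 1 list platelets among the routine blood tests without a unit.

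On planned enrolment, Section 5.1 says "so 15 participants are planned to be enrolled".

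**The concern.** Two cell counts in the same line are given in units that differ by a factor of one million, with the same power of ten in front of both. One of the two must be wrong, and it is the platelet limit that cannot describe a real blood count.

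This is a threshold that decides who enters the trial, not background text. Sub-item a) also carries no clinical-judgement qualifier. Sub-item b), by contrast, requires that the abnormality be clinically significant, so under b) the investigator has stated discretion and under a) there is none. Section 7.1 asks monitors to check compliance with the protocol, and Section 10 requires the trial to be run according to it. On the literal text, each enrolled participant meets an exclusion criterion. The exact wording of an eligibility rule should not have to be set aside for the rule to work.

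**Working it through.** The limit is a stated threshold and is not derived from other figures, so there is no calculation in the plan to reproduce. The check is a unit conversion.

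**Inputs**

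- Platelet limit as written: 75 × 10^9 per μL (Section 3.2.2 and program summary, item (5)a).
- Neutrophil limit in the same line: 1.50 × 10^9 per L.
- Planned enrolment: 15 (Section 5.1). This follows from the 12 completers and 15% dropout given there: 12 / (1 − 0.15) = 14.1, rounded up to 15.
- Conversions: 1 L = 10^6 μL; 1 μL = 10^9 fL.

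**Step 1. Is the mismatch an extraction effect?** The neutrophil limit lost its superscript in the same way and kept its per-litre unit. Losing a superscript does not turn a litre into a microlitre. Nor can 109 be meant as a plain number: the neutrophil limit would then be 1.50 × 109 = 163.5 cells per litre, which is absurd. So 10^9 is the only sensible reading, and the per-microlitre unit is in the source.

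**Step 2. Size of the discrepancy.**

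- As written: 75 × 10^9 per μL × 10^6 μL per L = 7.5 × 10^16 per L.
- Ratio to the per-litre reading: (7.5 × 10^16) / (75 × 10^9) = 10^6.

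**Step 3. Who meets the exclusion on a literal reading?** The protocol gives no platelet range, so the counts below are assumptions, chosen to be very wide.

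| Assumed count per L | Same count per μL | Written limit ÷ count | Excluded as written | Excluded if limit is per litre |
| --- | --- | --- | --- | --- |
| 10 × 10^9 | 10,000 | 7,500,000 | yes | yes |
| 75 × 10^9 | 75,000 | 1,000,000 | yes | no |
| 150 × 10^9 | 150,000 | 500,000 | yes | no |
| 450 × 10^9 | 450,000 | 166,667 | yes | no |
| 2,000 × 10^9 | 2,000,000 | 37,500 | yes | no |

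Every count in the range falls below the written limit, by a factor of at least 37,500. The literal result is therefore 15 of 15 planned participants.

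**Step 4. Could any count reach the written limit?** If a microlitre of blood held nothing but platelets, 75 × 10^9 of them would leave 10^9 fL / (75 × 10^9) = 0.013 fL each. That is far too small for a blood cell. The conclusion in Step 3 therefore does not depend on the range assumed.

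**Step 5. Do the natural repairs agree?**

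- Correct the unit and keep the exponent: 75 × 10^9 per L ÷ 10^6 = 75,000 per μL.
- Correct the exponent and keep the unit: 75 × 10^3 per μL = 75,000 per μL.

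Both repairs give the same count.

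**The case against.** The strongest reply is that this is a typing error with no realistic consequence. The value is impossible, so nobody could apply it literally. The two obvious corrections coincide, and the neutrophil limit beside it points the same way. The trial is single-centre, so one team screens for about 15 places and different sites cannot read the limit differently. No endpoint, visit, test schedule, sample size or analysis depends on it. The program summary probably just copies Section 3.2.2, which would make this one slip in two places rather than two independent errors.

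All of this stands as a statement about impact. A reader might go further than the protocol allows and infer that staff must guess the unit, that eligibility cannot be applied or audited, or that enrolment would stop. The documents do not support those readings: the repairs lead to one threshold, and nothing in the protocol indicates that a monitor would log deviations against a physically impossible unit. The 15-of-15 figure describes the literal text and is not a forecast of deviations.

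The reply does not remove the error. The intended unit is an inference from the neighbouring limit, because the protocol never states it. The criterion also leaves the investigator no written discretion to read it in another way.

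**Conclusion.** The platelet limit is wrong as written, by a factor of 10^6 relative to the per-litre reading, and it appears in both the program summary and Section 3.2.2. On a literal reading it excludes everyone. In practice it would probably be recognised and applied as 75,000 per microlitre, so the population enrolled would be the one intended if that is indeed the limit meant.

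The factor of 10^6 and the literal exclusion of every candidate rest only on the text and on arithmetic. Two points are judgement: that the intended limit is the per-litre figure, which the sponsor must confirm, and that the centre would notice the slip. This is a correction the sponsor should make because the text is an operative eligibility rule. It is not a threat to the trial's conclusions.

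**What to change.** The sponsor should confirm the intended platelet limit, then restate it in a unit consistent with the neutrophil limit in the same line. The change belongs in both Section 3.2.2, item (5)a), and the matching item in the program summary, so that the two stay in agreement.

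The edit is one unit symbol in two places. Section 10.1 requires revised protocols to go back to the ethics committee, so the added cost is a routine submission, which can be combined with any other amendment. Design, sample size and analysis do not change.

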**3.2.3 Exit Criteria**

**3.2.3.1 Withdrawal At The Investigator's Discretion**

(1) During the clinical trial, if the investigator determines that the subject is unsuitable to continue participating in this study.

(2) In the event of serious AEs, and if the investigator determines that continuing the study will not be beneficial.

(3) In cases where subjects experience serious AEs and are deemed unsuitable to continue participating in the research.

(4) When, following treatment administration, the subject exhibits poor medication compliance in the absence of AEs.

(5) If the subject participates in other concurrent clinical trials during this study.

(6) When other drugs that may impact tolerance and pharmacokinetic analysis and judgment are used during the trial.

(7) In the case of an unexpected pregnancy.

3.2.3.2 Voluntary Withdrawal by Paticipants

If the participants don't wish to continue participating in the clinical research, they have the right to withdraw from the study at any stage without facing discrimination or retaliation, as outlined in the informed consent form. Not explicitly expressing a desire to exit but ceasing to take medication, undergo testing, and becoming lost to follow-up are also considered forms of "dropping out" or "withdrawal." Possible reasons for withdrawal may include:

(1) The subject withdraws their informed consent.

(2) Circumstances prevent the subject from continuing to complete follow-up assessments on time for various reasons.

**3.2.4 Post-Exit Procedures**

The investigator should meticulously document the reason and timing of the subject withdrawal, conduct appropriate observations and assessments for withdrawn subjects according to the study plan, and complete the specified evaluations after the retreat.

These details should be recorded in the corresponding source documents, accompanied by a description of the reason for suspension.

Participants who quit the study should continue to be monitored for AEs. Negative event follow-up for these subjects should persist until their condition returns to baseline or until the investigator determines that further observation is unnecessary. Throughout the study, all participants who received medication but failed to complete the prescribed research activities outlined in the protocol should have their last test results considered as the outcome. Investigators should proactively reach out to those patients who did not comply with the requirements and maintain accurate records of these contact attempts in the corresponding source documents (e.g., including the time and date of telephone contact, proof of registered mail receipt, etc.), ensuring proper documentation.

No further data collection is necessary in the event of withdrawal for the following reasons: (1) the participants withdraw their informed consent; (2) the participants experience a fatal event; (3) the study is terminated.

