**Table 1 ASC22 clinical trial flow chart**

|  | **Screening perioda** | | **Treatment period** | | | | | | **Screening period** | | |
| --- | --- | --- | --- | --- | --- | --- | --- | --- | --- | --- | --- |
| **V1** | **V2** | **V3** | **V4** | **V5** | **V6** | **V7** | **V8** | **V9** | **V10** | **V11** |
| **Screening** | **Baseline** | **Week 2** | **Week 4** | **Week 6** | **Week 8** | **Week 10** | **Week 12** | **Week 16** | **Week 20** | **Week 24** |
| **Visit time** | **Day- 28~Day-2** | **Day 0** | **Day15**  **±2** | **Day 29**  **±2** | **Day 43**  **±2** | **Day 57**  **±2** | **Day 71**  **±2** | **Day 85±2 /Early termination** | **Day 113±5** | **Day 141±5** | **Day 169±2** |
| **Informed consent** | **×** |  |  |  |  |  |  |  |  |  |  |
| **Demographic** | **×** |  |  |  |  |  |  |  |  |  |  |
| **Medical history, treatment history, and history of drug abuse** | **×** |  |  |  |  |  |  |  |  |  |  |
| **Physical examination** | **×** | **×** | **×** | **×** | **×** | **×** | **×** | **×** | **×** | **×** | **×** |
| **Blood pregnancy test**  **(if applicable)** | **×** |  |  | **×** |  | **×** |  | **×** |  |  |  |
| **Height, weight, vital signsb** | **×** | **×** | **×** | **×** | **×** | **×** | **×** | **×** | **×** | **×** | **×** |
| **Blood routined** | **×** | **×a** | **×** | **×** | **×** | **×** | **×** | **×** | **×** | **×** | **×** |
| **Blood biochemistry**  **(including myocardial enzymes)e** | **×** | **×a** | **×** | **×** | **×** | **×** | **×** | **×** | **×** | **×** | **×** |
| **Urine routinef** | **×** | **×a** | **×** | **×** | **×** | **×** | **×** | **×** | **×** | **×** | **×** |
| **Coagulation functiong** | **×** | **×a** | **×** | **×** | **×** | **×** | **×** | **×** | **×** | **×** | **×** |
| **Thyroid functionh** | **×** | **×a** |  | **×** |  | **×** |  | **×** |  |  | **×** |
| **Adrenalinei** | **×** | **×a** |  | **×** |  | **×** |  | **×** |  |  |  |
| **Blood sugarj** | **×** | **×a** |  | **×** |  | **×** |  | **×** |  |  |  |
| **Twelve-lead electrocardiogramc** | **×** | **×** | **×** | **×** | **×** | **×** | **×** | **×** |  |  |  |
| **Chest CT scan** | **×** |  |  |  | **×** |  |  | **×** |  |  |  |
| **Cardiac ultrasound** | **×** |  |  |  | **×** |  |  | **×** |  |  |  |
| **Abdominal ultrasonography (B ultrasound)** | **×** |  |  |  | **×** |  |  | **×** |  |  |  |
| **Plasma HIV Viral load (HIV-1 RNA)** | **×** | |  | **×** |  | **×** |  | **×** |  |  |  |

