**6 Efficacy and safety outcomes**

The primary outcomes were assessed by quantifying changes in CA HIV RNA, total HIV DNA, integrated HIV DNA in PBMCs, and plasma HIV RNA, as well as by analyzing variations in the functionality of HIV Gag- and Pol- specific CD8+ T cells from baseline to post-treatments. In addition, changes in CD4+ T cell counts, CD8+ T cell counts, and CD4/CD8 ratios were monitored at baseline and at different time points during treatment.

Safety Outcomes: number of participants experienced with drug-related AEs of Grade 3 or Higher.

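### Section 3.2.4 makes the last test result the outcome for treated non-completers, so a baseline, early on-treatment or exit value can stand in for the post-treatment result

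*Protocol*

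**What the plan says.** Protocol section 3.2.4 sets a rule for those, and only those, who took study drug and then "failed to complete the prescribed research activities outlined in the protocol should have their last test results considered as the outcome". It names no endpoint, visit window or reason for leaving, and no alternative analysis. The same section asks for evaluations after exit. It waives further data collection only after withdrawal of consent, death or termination of the study.

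Section 6 defines the virological primary outcomes by "quantifying changes in CA HIV RNA, total HIV DNA, integrated HIV DNA in PBMCs, and plasma HIV RNA", together with HIV-specific CD8+ T-cell function, "from baseline to post-treatments". No week is named. Section 5.4.2 places cell-associated (CA) HIV RNA at 24 weeks.

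Table 1 marks plasma HIV RNA, T-cell counts, Gag-specific CD8+ T cells and HIV-1 DNA at screening/baseline and at Weeks 4, 8 and 12. It has no row for CA HIV RNA. The Week 12 column is headed "Day 85±2 /Early termination", so one visit serves both purposes.

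Section 3.2.3.1 lets the investigator withdraw a participant when "the subject exhibits poor medication compliance in the absence of AEs". Section 5.1 expects that "12 participants will complete the trial, and the dropout rate will be controlled within 15%, so 15 participants are planned to be enrolled".

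**The concern.** The trial has one arm and its primary outcomes are changes from baseline, so no control group shares the error that a carried value introduces. With markers taken every four weeks, the last test can predate the end of treatment by a month or more.

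The markers also need not move together. Under a shock-and-kill strategy, an activation marker such as plasma HIV RNA may rise and then fall, while HIV DNA falls later. One carry-forward rule can then understate one outcome and overstate another. Because poor compliance is a ground for withdrawal, who is carried forward may also depend on exposure to the drugs.

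The rule stands in the protocol itself, so it is not detail left to a statistical analysis plan. A plan that used observed data only would contradict it.

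**Working it through.** **1. The plan's own figure.** 12 completers with 15% dropout: 12 / (1 − 0.15) = 14.12, rounded up to 15. The stated enrolment reproduces.

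**2. How many values could be carried.** 15% of 15 is 2.25, so about 2. If exactly 12 complete, 15 − 12 = 3, which is 3/15 = 20% and exceeds the stated 15%.

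**3. What each kind of leaver contributes for the Table 1 markers.**
- Leaves early and attends the early-termination visit: a value from the day of exit.
- Leaves early and misses that visit, for example through loss to follow-up or withdrawn consent: baseline if lost before Week 4, the Week 4 value if lost between Weeks 4 and 8, the Week 8 value if lost between Weeks 8 and 12.
- Misses only Weeks 16–24: the Week 12 value already exists, so nothing is substituted at the end of treatment.

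**4. Effect on the mean change.** Let k of 15 values be carried and let f be the share of the final change already present at the last test. Suppose leavers would have had the same final change as completers. Then

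estimated change / true change = (15 − k + k·f) / 15.

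| f (assumed) | k = 2 | k = 3 |
|---|---|---|
| 0 (baseline carried) | 13/15 = 0.867 | 12/15 = 0.800 |
| 1/3 | 13.67/15 = 0.911 | 13/15 = 0.867 |
| 1 (last value equals final) | 1.000 | 1.000 |
| 2 (carried value twice the final change) | 17/15 = 1.133 | 18/15 = 1.200 |

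**5. Transient rise with no final change.** If the carried rise is r and the true final change is 0, the estimate is k·r/15. For an assumed r of 0.5 log10 in a marker sampled at Weeks 4 and 12, such as plasma HIV RNA, this is 2 × 0.5/15 = 0.07 log10 or 3 × 0.5/15 = 0.10 log10.

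**6. Effect on the test.** This was simulated with 40,000 runs, a one-sample t-test on change, SD of change 1, and two-sided 0.05. The protocol gives 0.05 without sidedness and gives no SD or effect size, so these are assumptions.
- True change 0, baseline carried for 3: mean 0, rejection rate 0.047.
- True change 0, values averaging +1 SD carried: rejection rate 0.061 with 2 carried and 0.084 with 3.
- True change 0.5 SD, baseline carried for 3: mean 0.40, power 0.35. The 12 completers alone give mean 0.50 and power 0.35.

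In this last setting the rule buys no power over the completers and costs a fifth of the estimated effect.

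**The case against.** The strongest defence is that the protocol limits the damage. The early-termination visit carries the Table 1 markers, section 3.2.4 asks for evaluations after exit, and withdrawal for poor compliance does not by itself end data collection. When baseline is carried, the error runs towards no change, which is conservative for a claim of reservoir reduction, and the false-positive rate is not raised. The sentence also sits among instructions on adverse-event follow-up and contact attempts, so its intended scope (efficacy, safety or both) is unclear. All of this stands. It narrows the problem without removing it: a participant lost to follow-up has no exit visit, an exit value is still not a Week 12 value, and unclear scope is itself a reason to amend.

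A reader might infer more than the documents support:
- That the rule covers every non-completer. It covers only those who received medication.
- That every primary change is biased. The bias is zero without dropout, for a flat marker, or when the last value equals the final one.
- That exit results will be analysed as Week 12. A shared column heading permits that but does not say it.
- That a Week 4 rise in CA HIV RNA would be carried to Week 12. Table 1 lists no CA HIV RNA sample, and section 5.4.2 names only Week 24.

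A mixed model is not free of assumptions either. It relies on data missing at random, which is doubtful if missingness follows exposure. Log-scale modelling also suits plasma HIV RNA poorly when entry requires results below 50 copies/ml.

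**Conclusion.** The point holds in this limited form and should be fixed. Section 3.2.4 sets an unrestricted last-value rule for treated non-completers. Followed as written, it can replace the post-treatment result with a baseline, Week 4, Week 8 or exit value.

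At about the stated dropout (2 of 15), the mean change is 87–91% of the truth when none or one third of the effect is present at the last test. With 3 of 15 it is 80–87%; that case goes beyond the stated 15% and should not be read as the expected one. If the carried value is twice the final change, the estimate is 113–120% of the truth. Size and direction therefore differ by marker.

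These figures rest on assumed effect shapes, on leavers having the same eventual change as completers, and on an end-of-treatment comparison that the protocol does not itself name.

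**What to change.** - Delete the sentence for the efficacy outcomes, or restrict it to a sensitivity analysis. If it was meant for safety only, say so.
- Name the primary time point, for example Week 12 for the Table 1 markers. Reconcile the 24-week CA HIV RNA assessment in section 5.4.2 with the change defined in section 6.
- Analyse observed values at their actual visits from all treated participants. A repeated-measures mixed model on log10 HIV DNA would serve. Use a method suited to values below quantification for plasma HIV RNA.
- Record early-termination samples at their actual study day and do not label them Week 12.
- State explicitly that consenting participants who stop study drug or are non-compliant keep the Week 4, 8 and 12 samples already scheduled.

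The cost is mainly protocol wording, a standard model, and some effort to retain participants for visits already planned. The downside is slightly fewer values at the primary time point and reliance on a missing-at-random assumption. Carry-forward as a sensitivity check would show how far the result depends on the handling of missing values.

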**3.2.5 Criteria for Terminating the Study**

Study termination may occur under the following circumstances:

(1) The subject experiences intolerable toxicity, and the investigator determines they are unsuitable to continue receiving the experimental drug.

(2) Significant errors are identified in the study protocol.

(3)The administrative department cancels the study.

Comprehensive suspension or termination of the study can be temporary or permanent. Please keep all study records for future reference in case of study suspension or termination.

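### Section 3.2.4 lifts data collection after study termination without an exception for adverse events, so dosed, consenting participants need not be followed for safety once the study stops

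*Protocol*

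**What the plan says.** Section 3.2.4 first sets a general duty. The investigator is to "conduct appropriate observations and assessments for withdrawn subjects according to the study plan", and "Participants who quit the study should continue to be monitored for AEs", lasting until return to baseline or until the investigator sees no need for more observation.

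Its closing paragraph then makes an exception: "No further data collection is necessary in the event of withdrawal for the following reasons". The first reason is withdrawal of consent; the others are "2) the participants experience a fatal event; (3) the study is terminated". The paragraph does not mention AEs and does not refer back to the general duty.

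Section 3.2.5 gives three grounds on which the study may be terminated. The first reads "The subject experiences intolerable toxicity, and the investigator determines they are unsuitable to continue receiving the experimental drug". The other two are serious protocol errors and cancellation by the administrative department. The section adds that a stop may be temporary or permanent and that records must be kept.

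Table 1 labels visit V8 "Day 85±2 /Early termination" and schedules AE collection again at Weeks 16, 20 and 24. Section 6 defines the safety outcome as a count of participants with a drug-related event of Grade 3 or worse.

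**The concern.** The three exempted situations are not alike. Consent withdrawal and death end data collection by their nature. Study termination does not: participants who have received ASC22 and chidamide can still be seen and have not asked to be left alone. Treating the three alike removes the protocol's requirement for safety follow-up where such follow-up is both possible and wanted.

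Two things are at stake. One is the care of participants with an event that is open, or still to come, when the study stops. The other is the safety outcome. In a small single-arm study it is a plain count of people, and an event not recorded after the stop does not enter it.

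**Working it through.** The protocol gives no figure to reproduce here. The check is a reading of the text, followed by a count of what the schedule holds after a stop.

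**1. Does the general AE duty survive a study stop?** There are two ways to read section 3.2.4.

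- If a participant in a terminated study counts as having withdrawn, which is how the closing paragraph treats it, both the general duty and the exemption apply. The exemption is the more specific of the two, covers data collection without limit, and does not preserve the duty.
- If such a participant does not count as having quit, the general duty does not reach them.

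On neither reading does the text clearly require AE follow-up.

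**2. Which stops are affected?** The exemption does not depend on the reason for termination. It covers all three grounds in section 3.2.5, and it does not separate a temporary stop from a permanent one. The gap therefore exists whether or not the first ground is a true study-level toxicity stop.

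**3. What remains in place?** Reading Table 1 generously, the V8 assessments are done at the stop as the early-termination visit. That is one assessment and captures events up to that date. It does not require an open event to be followed, nor later events to be collected.

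**4. What does the schedule hold after that visit?** Inputs are the Table 1 visit days: V8 on Day 85, Weeks 16, 20 and 24 on Days 113, 141 and 169, and the third ASC22 dose on Day 57.

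- AE contacts after V8: V9, V10 and V11, which is 3.
- Time from V8 to the last contact: 169 − 85 = 84 days.
- Time from the third dose to the last contact: 169 − 57 = 112 days.

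A participant stopped earlier has more of the calendar left: 169 − 29 = 140 days after the second dose, for instance. These figures describe the remaining schedule. They do not measure lost events.

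**5. Could events still matter after the stop?** Section 3.1.1 gives an average ASC22 half-life of about 8.3 days. The fraction of a single dose left after t days is 2^(−t/8.3). At t = 28 this is 2^(−28/8.3) = 2^(−3.37) ≈ 0.096, about 10%. The half-life comes from oncology phase I data for ASC22 alone and is assumed to apply here. Section 3.1.3 also reports a Grade 3 autoimmune dermatitis that took 33 days to resolve under treatment. Both make an event that outlasts a single visit plausible. Neither gives its probability.

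**6. Effect on the safety outcome.** Each participant whose only qualifying event goes unrecorded lowers the count by one. No expected number can be given, because the protocol states neither the chance of a stop nor an event rate for this combination.

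**The case against.** The other side has several fair points.

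- **The clause is permissive.** It says collection is not necessary; it does not forbid it. A reader might infer that the protocol bars AE follow-up after termination. It does not. This limits the point but does not remove it, since a protocol should state the minimum that is required, and here none is stated.
- **The general AE duty may still hold.** One can read section 3.2.4 as ending general data collection while AE monitoring goes on. That is tenable, but the text does not say so, and a participant whose study was stopped has not plainly quit.
- **The link to toxicity is weak.** A reader might infer that section 3.2.5 sets up a toxicity-driven study stop after which safety data are dropped. Its first ground is listed under study termination, but it is worded for a single subject coming off drug and overlaps with the individual exits in section 3.2.3.1, such as "During the clinical trial, if the investigator determines that the subject is unsuitable to continue participating in this study" and "In cases where subjects experience serious AEs and are deemed unsuitable to continue participating in the research". A toxicity stop of the whole study is one reading, by placement only. The gap does not depend on it.
- **Individual exits are covered.** A reader might infer that a participant who leaves alone because of toxicity also loses follow-up, or that no individual exit route for toxicity exists. Neither holds: section 3.2.3.1 supplies the route, and section 3.2.4 keeps such participants under observation.
- **Other safeguards exist.** Section 10 requires adherence to GCP and the Declaration of Helsinki, and V8 doubles as the early-termination visit. These help, but neither sets out follow-up of open or later events after a study stop.
- **The size cannot be quantified.** One participant out of 15 is 1/15 = 6.7%, but the outcome is defined as a count, and that conversion would suggest a bias that nothing in the document supports.

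**Conclusion.** The point holds as a drafting gap with a safety consequence. As written, once the study is terminated on any ground in section 3.2.5, dosed participants who still consent need not be followed for AEs beyond the early-termination visit. Drug-related events of Grade 3 or worse that are open then, or start later, may go unrecorded. For a stop at V8, what is no longer required is three scheduled AE contacts over 84 days.

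This rests on two assumptions: that the closing paragraph of section 3.2.4 is followed literally, and that the early-termination visit is still done at a study stop. The consequence is a possible undercount of participants in the safety outcome. It arises only if the study stops early, with a probability that the document does not give. Sample size, efficacy endpoints and dosing are unaffected. The change is worth making because it is short and the present rule gives a worse result for safety than the alternative.

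**What to change.** In section 3.2.4, limit the third exemption to efficacy and reservoir assessments. Add that, after study termination, all dosed participants who have not withdrawn consent complete the early-termination visit and are then followed for AEs until return to baseline, until the investigator judges more observation unnecessary, or to the planned Week 24 contact.

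Optionally, reword the first ground in section 3.2.5 at study level, for example as emerging toxicity that makes further dosing of participants unacceptable. Any numerical threshold is a clinical decision for the sponsor and the investigator. Section 3.2.3.1 needs no addition.

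The cost is one or two sentences in an amendment and, only if the study stops early, a few AE contacts per participant. After V8 these are the three already in the schedule.
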